### Sample size

Based on previous work, we assumed a minimum clinically important difference for the four metre walk speed of 0.1 m/s.^28^ Assuming a SD of 0.24 as seen in the English Longitudinal Study of Ageing,^47^ and a correlation between baseline and 6-month measures of 0.8, as seen in a recent trial of older people at risk of falls^48^ (a similar population to those who will be enrolled in this trial), a total of 66 participants would be needed (33 per group) to give 80% power to detect this difference at a two-sided alpha=0.05 in an analysis that is adjusted for baseline values. Recruiting 80 participants will allow for 17.5% drop-out (higher than observed in previous trials of spironolactone and of vitamin D in similar populations^49 50^) to give 66 participants at follow-up.

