### Assignment of intervention

Participants will be randomised on a 1:1 basis using an interactive web-based randomisation system (Sealed Envelope). Minimisation (with a 30% random element) will ensure balance across the two arms based on the following stratification variables: sex and baseline walk speed (≤0.6 or >0.6 m/s). The allocation sequence is prepared by Sealed Envelope and is concealed from the study team. Participants are allocated a pack number at randomisation; this pack number is used by the trial pharmacy to dispense prelabelled medication packs. Participants, the clinical team and the study team (including investigators, research nurses collecting outcomes data, senior statistician and trial manager) are blind to treatment allocation during the trial. For the independent data monitoring committee (IDMC), the statisticians preparing the report will be partially blind. This means that analysis will be conducted by arm, but the statisticians will not know the treatment allocation for each arm. They will become unblinded if the IDMC requests fully unblinded data. The randomisation system has functionality for emergency unblinding. This will only occur for valid medical or safety reasons where it is necessary for the treating clinician to know which treatment the participant has been receiving; the randomisation system is able to inform the treating clinician by email without unblinding other members of the study team or the participant.

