### Statistical analysis

A statistical analysis plan will document the planned analyses and will be finalised prior to database lock at the end of the trial. For the primary outcome (4 m walk speed at 4 months postrandomisation), the difference between arms will be tested through fitting a linear regression model that is adjusted for baseline four metre walk speed and sex. A suitable transform of the data (eg, the best fitting Box-Cox transform) will be applied to ensure the data are approximately normally distributed. The model will allow estimation of the difference between arms together with the 95% CI and p value for testing the null hypothesis of no difference. Continuous secondary endpoints will be analysed in a similar manner to the primary outcome. Binary secondary endpoints will be analysed with a logistic regression model. All models will be adjusted for the outcome under test at baseline, baseline 4 m walk speed and sex.

The following preplanned subgroup analyses will be performed for the primary outcome: age >75 years vs≤75 years, men versus women, baseline walk speed >0.6 m/s vs ≤0.6 m/s. In addition, a per-protocol analysis will be performed in participants with adherence to study medication ≥80%.

The primary analysis will be a complete-case analysis. In the event the mortality rate is >5%, we will perform a sensitivity analysis by imputing the worst score possible for the primary outcome (ie, 0 m/s) in participants who died before the 4-month visit. A further sensitivity analysis will be performed by imputing the primary outcome to the worst score possible in the event both mortality and withdrawal due to illness is >5%. If more than 10% of primary outcome data is missing after imputation for missing-ness due to death and withdrawal due to illness, a sensitivity analysis using multiple imputation via chained equations using the baseline covariates in the imputation model will be performed. Twenty imputed datasets will be used.

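### The 5% triggers for the 0 m/s sensitivity analyses take no account of arm, so on the plain reading up to 4 deaths, even all in one arm, prompt no death analysis

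*Protocol article*

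**What the plan says.** All the rules are in the last paragraph of the protocol article's Statistical analysis section.

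- **Primary analysis:** "The primary analysis will be a complete-case analysis". Anyone without a 4-month walk speed is left out, including those who died or withdrew through illness.
- **Deaths:** "In the event the mortality rate is >5%, we will perform a sensitivity analysis by imputing the worst score possible for the primary outcome", with 0 m/s given as that score for participants who died before the 4-month visit.
- **Deaths and illness:** a further worst-score analysis is done "in the event both mortality and withdrawal due to illness is >5" per cent.
- **Other missing data:** if more than 10% of the primary outcome is still missing after those steps, multiple imputation by chained equations follows, using the baseline covariates.

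The design figures come from two other sections. Sample size: "Recruiting 80 participants will allow for 17.5% drop-out". Assignment of intervention: "Participants will be randomised on a 1:1 basis using an interactive web-based randomisation system".

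**The concern.** Losing participants to death or illness distorts a two-arm comparison mainly when the arms lose different numbers or different kinds of people. A trial-wide rate does not measure that. Two deaths per arm and four deaths in one arm give the same rate, but they have very different consequences for the comparison.

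The participants are older people with sarcopenia and prefrailty or frailty. The Background section itself notes that some of metformin's actions could have adverse catabolic effects in the short term. An imbalance against metformin is therefore a possibility the plan should be ready for. Under the rule as written, a walk-speed benefit seen among survivors could be reported without the 0 m/s check that the sponsor itself chose for deaths.

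There are two further problems in the same paragraph. The second trigger can be read in two ways that give different results. And deaths that miss the triggers can pass into an imputation model that predicts a walk speed for them.

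**Working it through.** **Inputs from the documents.** 80 randomised 1:1, so 40 per arm. Target effect: "we assumed a minimum clinically important difference for the four metre walk speed of 0.1 m/s". Spread: "Assuming a SD of 0.24 as seen in the English Longitudinal Study of Ageing". Correlation: "a correlation between baseline and 6-month measures of 0.8". Planned loss 17.5%, leaving 66.

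**Assumption.** The documents give no expected 4-month walk speed. Entry requires a baseline below 0.8 m/s and minimisation splits at 0.6 m/s. I take a metformin survivor mean of 0.6 to 0.8 m/s and also show 0.5 to 0.9.

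**Step 1: the plan's own figure.** The baseline-adjusted SD is 0.24 × √(1 − 0.8²) = 0.144. For 0.1 m/s at two-sided 0.05 and 80% power this gives 33 per arm, 66 in total (power at 33 per arm: 80.5%). Then 66/0.825 = 80. The stated sample size is reproduced.

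**Step 2: when the death trigger is met.**

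| Deaths | Rate among 80 | Above 5%? | Rate in one arm of 40 if all fall there |
|---|---|---|---|
| 3 | 3.75% | no | 7.5% |
| 4 | 5.0% | no | 10% |
| 5 | 6.25% | yes | 12.5% |

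**Step 3: what the omitted analysis would show, 4 metformin deaths and 0 placebo deaths.** Scoring the deaths 0 m/s lowers the metformin mean by m × 4/(s + 4), where m is the survivor mean and s the number of measured metformin survivors. I use s = 36 (no other loss) and s = 33 (planned evaluable number).

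| m (m/s) | Fall, s = 36 | Effect left of 0.10 | Fall, s = 33 | Effect left of 0.10 |
|---|---|---|---|---|
| 0.5 | 0.050 | 0.050 | 0.054 | 0.046 |
| 0.6 | 0.060 | 0.040 | 0.065 | 0.035 |
| 0.7 | 0.070 | 0.030 | 0.076 | 0.024 |
| 0.8 | 0.080 | 0.020 | 0.086 | 0.014 |
| 0.9 | 0.090 | 0.010 | 0.097 | 0.003 |

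So 60% to 86% of the effect goes at means of 0.6 to 0.8, and 50% to 97% at 0.5 to 0.9.

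**Step 4: check in the adjusted model.** I simulated 3,000 trials with the plan's SD, correlation and effect, and an assumed baseline mean of 0.6 m/s. The baseline-adjusted estimate fell from 0.100 to 0.029 m/s (36 metformin survivors, 40 placebo) or to 0.024 m/s (33 and 33). The chance of a significant benefit fell from 84% to 3% and from 78% to 2%.

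**Step 5: 3 versus 0.** With m = 0.7 and 37 survivors the fall is 0.7 × 3/40 = 0.0525, about 53% of the effect. At 3.75% this is also below the trigger.

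**Step 6: the second trigger, with 4 deaths and 10 illness withdrawals.** Deaths are 4/80 = 5.0%, illness withdrawals 10/80 = 12.5%, together 14/80 = 17.5%.

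- If each rate must exceed 5%, deaths do not, and no worst-score analysis runs. Nothing has been imputed, so 17.5% is missing, the 10% rule is met and multiple imputation runs. As written it covers the 4 deaths and predicts their walk speeds from baseline covariates.
- If the combined rate is meant, 17.5% exceeds 5% and the worst-score analysis runs.

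**The case against.** The strongest defence is that scoring death as 0 m/s answers a different question from the complete-case comparison. The fall from 0.10 m/s is then a consequence of that scoring and not a measured bias, and keeping such an analysis for non-trivial mortality is a defensible choice. The first half stands: the figures show how much the omitted check could matter, not how wrong the primary estimate is. The second half does not rescue the rule, because 10% mortality in one arm is not trivial and still misses a trial-wide trigger.

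Other limits stand and belong with the point:

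- The article does not say whether the mortality rate is trial-wide. That is the plain reading, but a per-arm rate (4/40) would trigger the analysis.
- The 4-death example sits on the boundary. With 79 randomised, 4 deaths are 5.06% and trigger; 3 deaths (3.8%) still would not.
- A 4–0 split is uncommon. Given 4 deaths and no effect on mortality, its probability is about 12% in either direction and about 6% against metformin.
- The direction matters. Four placebo deaths would raise the scored effect to about 0.16 m/s, at a placebo mean of 0.6.
- Follow-up is 4 months, short life expectancy is an exclusion, and home visits should limit illness-related loss. The documents give no expected mortality.

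A reader might infer that 4 deaths plus 10 illness withdrawals trigger nothing, or that survivors-only results would have no planned check at all. The documents do not support either. At 17.5% missing, multiple imputation runs if no worst score has been assigned, and on the combined reading the worst-score analysis runs. What can be absent is a worst-score check.

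Nor should by-arm reporting of deaths be called a gap. Adverse events are recorded at every visit, the monitoring committee reviews data by arm, and the SAP, not shown here, may cover the rest.

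**Conclusion.** The concern holds in a limited form. The article fixes triggers that ignore arm. On the plain trial-wide reading with 80 randomised, up to 4 deaths prompt no death analysis however they are split. If all 4 were on metformin, the omitted analysis would have reduced a 0.10 m/s effect to roughly 0.01 to 0.04 m/s; the size rests on the assumed survivor mean. The second trigger needs one meaning, and the multiple-imputation step can, as written, give walk speeds to people who died, contrary to the 0 m/s score the plan otherwise assigns them.

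This affects sensitivity analyses, not the primary test. It is worth correcting because the result is meant to support a larger trial and the data needed are already collected.

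**What to change.** In the SAP, which the article says will be finalised before database lock:

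1. Remove both 5% triggers. Run the planned 0 m/s analysis for deaths, and the one for deaths plus illness withdrawals, whenever any such event occurs. This also removes the ambiguity over *both*.
2. Show deaths and illness withdrawals by arm beside these results.
3. State that walk speeds for participants who died are not imputed from baseline covariates in the multiple imputation.

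A rank-based version with deaths ranked lowest is optional.

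The cost is a few sentences and one table, with no new data. The drawback is that the analysis may rest on few events and be imprecise. In a simulation of 80 participants with a baseline mean of about 0.65 m/s, 5 zeros placed at random raised the standard error from about 0.032 to 0.051 and cut power from 86% to 43%. The result should be read as a check on direction and robustness, not as a second test of efficacy.

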### Trial oversight

A trial management group (TMG), facilitated by NCTU, will convene approximately monthly throughout the duration of the trial. Members will consist of key NCTU staff, the Chief Investigator, coapplicants, trial statisticians, local site research staff and a Sponsor representative. A patient and public involvement representative will attend TMG meetings at a frequency determined on an ongoing basis. The TMG undertakes, with the additional of external membership, the role of a Trial Steering Committee for this small, relatively low risk CTIMP study. An IDMC has been appointed to provide an independent review of participant safety. The independent members comprise two clinicians and a statistician. The IDMC will meet at least annually, and report directly to the TMG.

### Patient and public involvement

A patient panel (convened by VOICE Global) consisting of older people with lived experience of muscle weakness was involved in the design of the trial protocol, selection of outcome measures and reviewed the PIS. A lay member (SC) sits on the TMG and is involved in the overall management of the trial and in dissemination plans for the results.

### Harms

Data from all AEs will be recorded on the trial database at every trial visit. Serious AEs (SAEs) will be assessed for any relationship to the treatment intervention (causality), by a delegated, medically qualified site doctor. The following SAEs will be recorded on the database, but do not require reporting to Sponsor: any death or hospitalisation due to a new cardiovascular event, new diagnosis or treatment of cancer, fall or fracture, infection, delirium, reduced mobility, exacerbation of an existing medical condition, admission for elective or planned investigation or treatment, or hospitalisation due to nausea, vomiting, constipation or diarrhoea. The above exceptions to immediate SAE reporting refer only to SAEs where the trial medication is not deemed to be causally related to the event by the local site principal investigator. The chief investigator will assess, on behalf of sponsor, expectedness (by reference to the approved reference safety information) of any SARs.

Safety assessments will be conducted at screening and at the 1, 2, 3 and 4 months follow-up visits. Key safety data will include serum creatinine concentrations—eGFR will be calculated to ensure adequate renal function (>30 mL/min/1.73 m^2^), LFTs, blood glucose and blood lactate concentrations. Lactate levels of >4 mmol/L will lead to discontinuation of trial medication.

### Consent

Informed, written consent will be sought at the screening visit, prior to conducting any trial procedures, including screening assessments. Where the screening visit takes place in the participant’s home, the informed consent discussion with a delegated local investigator may take place in person or remotely by telephone, teleconference or videoconference. A delegated research nurse will be present in the participant’s home to facilitate this, and to countersign the consent form. The investigator will complete, date and sign a consent interview proforma to provide a comprehensive account of the remote consent interview.

### Ancillary and post-trial care

No provision for continuation of trial medication will be made by the trial team or sponsor. Metformin is not licensed for the indication under study in this trial; any off-licence use of metformin after the end of the trial would be the responsibility of the participant’s usual primary or secondary care clinical team. Participants and their GP will be informed by letter of which treatment they took after all participants have completed their final visit and the database is locked.

## Ethics and dissemination

### Ethics approval

A favourable ethical opinion has been granted from the UK Health Research Authority Research Ethics Committee (North-West-Liverpool Central Research Ethics Committee; trial reference approval number 20/NW/0470). The trial has also received approval from the UK Medicines and Healthcare products Regulatory Agency (MHRA; trial reference number 2020-004023-16). The trial has been included in the National Institute for Health and care Research Clinical Research Network (NIHR CRN) portfolio (NIHR CRN study ID: 47772). The trial Sponsor is the Newcastle Upon Tyne Hospitals NHS Foundation Trust, Freeman Hospital, [name]. The trial Sponsor has delegated responsibility for trial management to NCTU, including trial design; review and approval of all localised patient-facing documentation prior to implementation at each site; collection, analysis and interpretation of data; writing of the protocol publication and final clinical report manuscripts. This protocol manuscript is based on V.7.0 of the trial protocol (dated 13 December 2021)

### Dissemination policy

A final report of the trial will be provided to the Sponsor, Research Ethics Committee and the trial Funder within 1 year of the end of the study. The trial results will be uploaded to the European Union Drug Regulating Authorities Clinical Trials (EudraCT) database, as per the European Commission’s guidelines on posting and publication of result-related information within 12 months. The trial is registered on the ISRCTN trial database and trial results will be made publicly available on the ISRCTN trial registry within 12 months of the end of the trial, defined as Last Patient Last Visit date.

The final clinical trial report will be used for publication and presentation at scientific meetings. Summaries of results will also be made available to investigators for dissemination within their clinical areas and to the wider public, and a summary of results will be sent to all participants along with their treatment allocation. If feasible within pandemic meeting restrictions, we will hold a dissemination event for participants and their families to present and discuss the study results.

### Access to data

Access to the full blinded dataset will be limited to the TMG and to authors of the trial publication. At the end of the trial, a deidentified dataset will be prepared and stored by Newcastle University. Requests for data sharing with study teams outside Newcastle University or the study Sponsor, including international requests, will be considered by a data access committee with representation from the funder, sponsor and the trial chief investigator.

## Discussion

Randomised controlled trials of treatments for sarcopenia and physical frailty are challenging to perform; previous trials have struggled to recruit their anticipated target numbers within the allocated time.^52^ This is in part because sarcopenia (and to a lesser extent physical frailty) are not diagnoses commonly made or recorded in clinical practice and thus identifying people with these conditions is not straightforward. In addition, people with sarcopenia usually have multimorbidity^53^ and by definition have components of the physical frailty syndrome. As a result, they may find it difficult to take part in clinical trials unless these trials are designed to facilitate their inclusion and retention.

We have sought to broaden the range of recruitment strategies employed to identify patients with sarcopenia and physical frailty. MET-PREVENT is one of the first sarcopenia trials to use a sarcopenia registry^31^ to facilitate recruitment, and we also build on recent work deploying measures of muscle strength and walk speed into routine clinical practice to facilitate recruitment. Although recruitment through primary care lacks specificity for identifying those with sarcopenia or physical frailty, the use of the eFI can improve the specificity of searches, and large numbers of potentially eligible participants can be reached via this route. We have aimed to minimise the burden of study visits in MET-PREVENT, both in terms of visit duration and tasks to complete during each visit, but also by providing a flexible approach to the venue in which study visits are undertaken. Many patients with sarcopenia or physical frailty find it difficult to travel to study centres and some are unable to leave their home at all. Our flexible approach to study visits with many of them taking place in the homes of participants enables this group of patients who would normally be excluded from participation to take part in research.

Although the trial is powered to detect the minimum clinically important difference in four metre walk speed, it is not powered to detect clinically important differences for some of the secondary outcomes. However, the trial seeks to provide proof-of-concept for a larger, multicentre trial that would be powered to detect differences in these outcomes, including transitions from physical prefrailty to frailty. The trial population excludes some groups for safety reasons (eg, those with chronic kidney disease) which limits the generalisability of the results. Muscle biopsies are not being performed, thus direct information on changes in skeletal muscle structure and function will not be obtainable from this trial.

The collection of blood and stool samples for future mechanistic analyses will maximise the scientific value of the trial but also look to identify those groups that may be more likely to benefit from metformin as an intervention in a future large trial. In addition, the mechanistic analyses (which will be performed after the main trial is complete) will identify which mechanistic pathways are most important in mediating any benefit of metformin and in doing so will help us identify pathways and featured targets for other interventions to prevent or treat sarcopenia and physical frailty. We believe that this study design provides a template for other phase II intervention trials for sarcopenia and physical frailty; this template should both accelerate progress in translational research and also enable easier comparison of results across different trials.^54^
